## Abstract

**Background:**

Neurocognitive deficits (NCDs) and associated meta-cognition difficulties associated with chronic substance use often delay the learning and change process necessary for addiction recovery and relapse prevention. However, very few cognitive remediation programs have been developed to target NCDs and meta-cognition for substance users. The study described herein aims to investigate the efficacy of a multi-component neurocognitive rehabilitation and awareness program termed “Neurocognitive Empowerment for Addiction Treatment” (NEAT). NEAT is a fully manualized, cartoon-based intervention involving psychoeducation, cognitive practice, and compensatory strategies relevant across 10 major cognitive domains, including aspects of attention, memory, executive functions, and decision-making.

**Method/design:**

In a single-blind randomized controlled trial (RCT), 80 female opioid and/or methamphetamine users will be recruited from an addiction recovery program providing an alternative to incarceration for women with substance use-related offenses. Eight groups of 9–12 participants will be randomized into NEAT or treatment-as-usual (TAU). NEAT involves 14 90-min sessions, delivered twice weekly. The primary outcome is change in self-reported drug craving from before to after intervention using Obsessive Compulsive Drug Use Scale. Secondary and exploratory outcomes include additional psychological, neurocognitive, and structural and functional neuroimaging measures. Clinical measures will be performed at five time points (pre- and post-intervention, 3-, 6-, and 12-month follow-up); neuroimaging measures will be completed at pre- and post-intervention.

**Discussion:**

The present RCT is the first study to examine the efficacy of an adjunctive neurocognitive rehabilitation and awareness program for addiction. Results from this study will provide initial information concerning potential clinical efficacy of the treatment, as well as delineate neural mechanisms potentially targeted by this novel intervention.

**Trial registration:**

ClinicalTrials.govNCT03922646. Registered on 22 April 2019

## Background

Opioid use disorder (OUD) and methamphetamine use disorder (MUD) are among the costliest mental health disorders in the USA and worldwide [1, 2]. Opioids (including prescription pain relievers and the illicit drug heroin) were involved in more than 42,000 deaths in the USA in 2016, more than any year on record [3]. This accounts for more deaths than road accidents and gun violence combined. In 2017, amphetamine use disorders were reported as the second most common use disorders worldwide by the United Nations Office on Drugs and Crimes (UNODC) [4]. Even more alarming, the number of overdoses with heroin and methamphetamine has tripled from 2011 to 2016 [5].

Chronic OUD and MUD are associated with numerous other mental health symptoms, including anxiety and depression [6, 7], as well as subjective and objective neural and cognitive deficits. These neurocognitive deficits (NCDs) are apparent across domains of memory, attention, decision-making, judgment, negative affect, metacognition, self-regulation, and impulse inhibition [8–10]. Neuroimaging studies indicate that these deficits may relate to dysfunction within a broad network of the brain regions, including the prefrontal cortex, orbitofrontal cortex, amygdala, nucleus accumbens, hippocampus, and anterior cingulate gyrus [11–13]. Maladaptive neural changes in these regions result in aberrant salience attribution, increased reward expectancy, changed learning pattern (including conditioned-incentive learning, habit learning, declarative learning), and impulsive decision-making [13].

Current treatment programs for OUDs and MUDs are mainly focused on abstinence from illicit drugs, with the assumption that the NCDs will be subsequently restored. However, NCDs are found to persist or sometimes even become exacerbated after long-term abstinence and are thought to contribute to relapse, decreased quality of life, and/or lack of reintegration into society [14]. Furthermore, NCDs (particularly those related to attention and memory) are considered a potential predictor for treatment outcomes for either the core substance use disorder or co-occurring symptoms (i.e., cognitive-behavioral therapies) [15, 16].

Numerous cognitive rehabilitation programs have been developed to focus on compensatory strategies and restorative exercises for NCDs associated with traumatic brain injuries [17], stroke [18], multiple sclerosis [19], and schizophrenia [20]. These programs have consistently been found to improve functioning and long-term outcomes for these groups of patients. There have been a few preliminary attempts to transplant cognitive rehabilitation programs for use with substance use populations, providing initial evidence that such programs could be beneficial. However, these programs did not explicitly link the cognitive rehabilitation modules to the processes involved in addiction and recovery. There is potential value in clarifying how such strategies may relate to the current neuroscientific understanding of addiction and recovery, as well as the co-occurring symptoms often experienced.

The present pilot study aims to characterize the clinical potential for an intervention targeting NCDs in OUDs and MUDs by enhancing awareness and use of neurocognitive skills in the context of substance use recovery. This aim will be accomplished by randomizing subjects who are already enrolled in substance use treatment to complete a novel “Neurocognitive Empowerment for Addiction Treatment” (NEAT) program or treatment-as-usual intervention. NEAT is novel in (a) its use of cartoons, brain awareness games, and real-life scenarios to ensure it is interactive and engaging; (b) its focus on the role of neurocognitive deficits in recovery from substance use and co-occurring mental health symptomatology; and (c) its incorporation of neuroscience findings specific to substance use.

The primary outcome in this trial is “change in self-reported drug craving from baseline to after intervention using the Obsessive Compulsive Drug Use Scale (total score) [21]. Secondary outcome is the mean change in self-report subjective cognitive functioning from baseline to after intervention using PROMIS Cog Abilities [22] and PROMIS Cog General measures [22]. Exploratory outcomes include additional psychological, neurocognitive, and structural and functional neuroimaging measures and are available on ClinicalTrials.gov. We hypothesis that as compared to the active control, the NEAT program will be associated with the following:
Greater reduction in self-report drug carving symptom from before to after intervention (primary outcome)Enhanced subjective cognitive functioning from before to after intervention (secondary outcome)Improved objective neuropsychological functioning from before to after interventionReduced mental health (i.e., depression and anxiety) symptoms from before to after intervention and other follow-up time pointsLower number of relapses as measured with urine drug tests during follow-up time pointsDecreases in subcortical limbic (amygdala and ventral striatum) activation and increase prefrontal cortical top-down inhibitory activation during induced drug craving in fMRI drug cue reactivity from before to after interventionIncreases in cortical gray matter density (measured with voxel-wise brain morphometry) and white matter track integrity (measured with fractional anisotropy) in areas related to self-control and awareness, including prefrontal gray matter and frontostriatal/frontoamygdalar white matter from before to after intervention

Outcome measures 3 to 7 are exploratory.

## Methods/design

### Study objectives

The present study aims to (a) determine the potential clinical impact of the NEAT program on clinical symptoms and function, from pre- to post-intervention and at long-term follow-up (12 months after treatment completion), and (b) explore the potential impact of the NEAT program on functional and structural brain recovery, from pre- to post-intervention.

### Research environment/context

The present trial is conducted by Laureate Institute for Brain Research (LIBR), and participants are recruited from a single site, the Women in Recovery (WIR) program at Family and Children’s Services located in Tulsa, OK. WIR is an intensive outpatient alternative for eligible women facing long prison sentences for non-violent drug-related offenses.

### Design

This is an assessor-blinded, two-arm, parallel-group, randomized controlled clinical trial formulated in accordance with the Consolidated Standards of Reporting Trials (CONSORT) 2010 guidelines (supplementary file 1). This protocol was written using the Standard Protocol Items: Recommendations for Interventional Trials (SPIRIT) guidelines, and the SPIRIT checklist is provided in supplementary file 2. Eighty participants will be recruited in eight groups. Groups will be randomly allocated to the intervention (*n* = 40) and control (*n* = 40) groups in blocks of 4 in a 1:1 ratio. All 80 participants will receive treatment-as-usual (TAU). Those subjects allocated to the intervention group will receive TAU but will complete NEAT in lieu of nonessential aspects of the TAU program that do not explicitly target neurocognitive function (e.g., culinary or legal education classes). Thus, both NEAT and TAU groups received similar amount (e.g., intensity, duration, frequency) of intervention. Self-report, interview-based, and neuroimaging assessments will be performed before (pre; week 0), during intervention (from week 1 to week 7), after the intervention period (post; week 8), and/or after a follow-up period (3, 6, 12 months; weeks 20, 32, 56, respectively). Interview-based assessments were conducted by a trained clinical practitioner blind to the allocation of participants. Figure 1 summarizes the full design of the trial in accordance with the CONSORT flow diagram.

**Fig. 1 Fig1:**
[figure not shown]
CONSORT flow diagram. The flow chart depicts participant progression through the study from the initial enrolment to allocation, follow-up, and finally analyses of their data stages. Planned sample size, *n* = 64; to be enrolled, *n* = 80. Forty participants will be enrolled in each arm (expected to be 8 dropouts in each arm from pre- to post-intervention on average)

The trial was approved by the Western Institutional Review Board (approval number: 20181028, 1-1141403-1) and registered in ClinicalTrials.gov on 22 April 2019 with NCT03922646 as ClinicalTrials.gov identifier no.; amendments have been made to the protocol since the original submission to ClinicalTrials.gov. The study is funded by the Oklahoma Center for Advancement of Science and Technologies (OCAST) [name] [HE], principal investigator [PI], and [name] [RA] as co-investigator [CI].

As this study is considered a “no or minimum risk” trial, there is no independent data monitoring committee (DMC) assigned for this trial. Trial investigators will monitor the data collection process, fidelity of the intervention, and integrity of protocol implementation on regular weekly basis meetings with the research staff. There is no plan for interim analyses, and there are no anticipated formal stopping rules for the trial as there are no anticipated problems that could be detrimental to the participants or the study integrity. The data that will be collected in this study will be available from the principal investigator on reasonable request.

### Participants

#### Inclusion criteria

To participate in this trial, subjects must (1) be 18 and 55 years old; (2) enrolled in WIR within 6 months; (3) diagnosed with OUD and/or MUD (based on the Mini-International Neuropsychiatric Interview (MINI) diagnostic interview for DSM-5 [23]) over the last 12 months; (4) be able to provide written informed consent; (5) have sufficient proficiency in the English language to understand and complete interviews, questionnaires, and all other study procedures; and (6) have completed at least an 8th grade education, to help facilitate the ability to engage in the written materials included in the NEAT program.

#### Exclusion criteria

Potential subjects will be excluded if they (1) are reluctant or unable to complete any of the major aspects of the study protocol, including self-report or behavioral assessment; (2) have uncorrectable vision or hearing problems that would interfere with the completion of the study procedures; (3) have diagnoses of schizophrenia spectrum or other psychotic disorders; (4) have current mental or physical health symptoms that require immediate attention (such as suicidal ideation with intent or plan, active psychotic symptoms, delirium); (5) have a history of unstable liver or renal insufficiency; glaucoma; significant and unstable cardiac, vascular, pulmonary, gastrointestinal, endocrine, neurologic, hematologic, rheumatologic, or metabolic disturbance; or any other condition that, in the opinion of the investigator, would make participation not be in the best interest (e.g., compromise the well-being) of the subject or that could prevent, limit, or confound the protocol-specified assessments; (6) have a positive test for drugs of abuse at the time of baseline assessment, including alcohol, cocaine, marijuana, opiates, amphetamines, methamphetamines, phencyclidine, benzodiazepines, barbiturates, methadone, and oxycodone; (7) have MRI contraindications; and (8) have moderate to severe traumatic brain injury (loss of consciousness for less than 30 min or > 24 h posttraumatic amnesia) or other neurocognitive disorder with evidence of neurological deficits, neurological disorders, or severe or unstable medical conditions that might be compromised by participation in the study. There is no limitation in the medications that participants could receive before, during, and after intervention. However, the list of medication will be recorded for exploratory analysis.

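### In exclusion criterion (8), the loss-of-consciousness limb of the brain-injury definition runs against both the severity label and the amnesia limb

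*Protocol article*

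**What the plan says.** The Exclusion criteria section of the protocol article opens with "Potential subjects will be excluded if they", so meeting any listed item removes the candidate. Item (8) names traumatic brain injury of a stated severity and begins to define it in a parenthesis: "moderate to severe traumatic brain injury (loss of consciousness for less than 30 min". The parenthesis has two limbs:

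- Consciousness limb: "loss of consciousness for less than 30 min".
- Amnesia limb: "or > 24 h posttraumatic amnesia".

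The same item then adds a wider clause, "or other neurocognitive disorder with evidence of neurological deficits", and goes on to neurological disorders and to severe or unstable medical conditions. Separately, item (5) ends with a discretionary clause, "or any other condition that, in the opinion of the investigator", which covers conditions that could confound the planned assessments.

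The article does not restate, define or correct the brain-injury threshold anywhere else.

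**The concern.** A parenthesis that defines a severity grade should pick out the more serious cases on each of its measures. Here one measure qualifies when it is long and the other when it is short, although both are offered as alternative signs of the same grade. This can be seen from the sentence alone, without any outside grading scale.

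What is at stake is the enrolled population. The intervention targets neurocognitive deficits. The secondary outcome is subjective cognitive functioning, and the exploratory outcomes include neuropsychological testing, gray matter density and white matter integrity. The Statistical analysis section also adjusts for IQ and plans subgroups by baseline neuropsychological and fMRI characteristics. Earlier brain injury is an obvious source of unwanted variation in all of these.

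A rule followed as printed could cost the trial in two ways. It could turn away women whom the label does not describe, at a single site that has to supply 80 participants. It could also leave some women whom the label does describe to be caught, or missed, by less specific clauses. The trial has little precision to spare: the Sample size calculation section puts the effective sample size between 10.3 and 23.7 per group.

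**Working it through.** No sample-size, power or alpha figure depends on this point, so there is no plan figure to reproduce. The check is a literal reading of the rule.

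**Inputs, all from criterion (8):**

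- Label: moderate to severe injury.
- Consciousness limb: duration L below 30 min, which is an upper bound.
- Amnesia limb: duration A above 24 h, which is a lower bound.
- Connective: or.

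**Rule as printed:** the injury is excluded if (L < 30 min) or (A > 24 h).

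**Example values put through the rule:**

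| Loss of consciousness | Amnesia | Consciousness limb | Amnesia limb | Excluded by this definition? |
|---|---|---|---|---|
| 5 min | 24 h or less | met | not met | yes |
| 60 min | 24 h or less | not met | not met | no |
| 5 min | more than 24 h | met | met | yes |
| 60 min | more than 24 h | not met | met | yes, by amnesia only |

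**Reading the table:**

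1. In the first two rows amnesia is held at 24 h or less. Lengthening the loss of consciousness from 5 to 60 min moves the candidate from excluded to not excluded. A severity definition should not move in that direction.
2. In the last two rows amnesia exceeds 24 h. The candidate is excluded whatever the duration of unconsciousness, so the consciousness limb makes no difference. The contradiction therefore matters only for candidates with amnesia of 24 h or less.
3. A no in the last column means only that the parenthesis does not exclude her. The wider clause in the same item, "24 h posttraumatic amnesia) or other neurocognitive disorder with evidence of neurological deficits", or the discretionary clause in item (5), could still do so. Neither clause can reverse the first row, because a candidate who meets one exclusion item is out.

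**Is it an artefact of text extraction?** No. The direction of the consciousness limb is spelled out in words, so a lost or swapped symbol does not explain it.

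**Size.** A count of affected women would need three things: the number screened, the proportion with a history of loss of consciousness, and the split by duration and amnesia. The article gives none of them. The figure of 80 is planned enrolment, not the number screened, and women wrongly turned away would not be among the 80.

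**The case against.** The strongest reply is that this is a drafting slip with little practical effect. The label states the intent, and a screener would probably notice that the parenthesis contradicts it. The Design section says that the protocol was approved by a review board and has been amended since registration. That document is not shown and may carry different wording. The article has other evident slips, such as the garbled age range in the Inclusion criteria. The primary outcome is self-reported craving, while brain structure and objective cognition are exploratory only.

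Much of this stands. Nothing shows that the printed rule was the one applied at screening. But the article does not leave the threshold to another document. It prints one, and that one contradicts its own label. Recruitment began in January 2019 according to the Trial status section, so women may already have been screened under it.

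Three stronger readings are tempting, and the document does not support them:

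- **Everyone with a history of loss of consciousness is misjudged.** A reader might infer this from the inverted limb. It does not follow, because anyone with more than 24 h of amnesia is excluded as the label intends.
- **Serious injuries are simply let in.** This holds for the consciousness limb alone. The amnesia limb, the wider disorder clause and investigator discretion are other routes to exclusion.
- **A number of affected participants can be given.** Multiplying an assumed prevalence by 80 would rest on a figure that the article does not supply and on the wrong denominator.

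**Conclusion.** The criterion is wrong as printed: one limb of the definition contradicts both the label it defines and the limb beside it. The printed rule goes astray only where amnesia is 24 h or less. There it excludes brief losses of consciousness and does not itself exclude long ones.

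The same rule applies to both arms, and the Randomization and blinding section keeps participants and research staff blind to condition until baseline assessments are complete. A reader might infer bias in the comparison of craving, but nothing in the document supports that. The harm is to the definition of the study population, to the precision of the cognitive and imaging measures, and to anyone who reuses the criterion in the larger trial that the article anticipates.

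The conclusion about the wording rests on the text alone. Any effect on enrolment depends on the printed wording having been used at screening, which the article does not show. The size of that effect cannot be estimated from the document. The point deserves correction but does not threaten the primary analysis.

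**What to change.** 1. Compare criterion (8) with the full approved protocol and the screening form. Reconcile the consciousness limb with the severity label and the amnesia limb, with the clinical lead confirming the threshold. This review proposes no cut-off.
2. Correct the wording in the article and in any other trial document that carries it.
3. Check the screening log for candidates with a history of head injury. Report how many, if any, were enrolled or excluded because of the printed wording. If staff worked from a correctly worded form, say so.

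The cost is a change of a few words and one pass through the screening log. The design, sample size and analysis model do not change.

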### Sample size calculation

With total enrollment of *N* = 80 and an estimated 20% attrition rate, we anticipate having complete data at our primary endpoint (post-treatment) for 32 subjects per group or 64 in total. Due to cluster randomization, the effective sample size will be *n* = (*mk*)/[1 + *ρ*(*m* − 1)] where *m*, *k*, *ρ* are the number of subjects per cluster, the number of clusters, and the intra-cluster correlation, respectively [24]; here, *k* = 4, and on average, *m*= 8 (80% of 10) per cluster. Considering a range of 0.05 to 0.3 for *ρ*, *n*_Eff_ will be somewhere between 10.3 and 23.7 per group. This effective sample size will provide a precision of *t*_*n*-1,1-*α/2*_/√*n* or 0.43–0.70, times standard deviation as margin of error at 95% confidence for a continuous measure (self-reported drug craving), and 80% power to detect large effect sizes (*d* = 0.83 to 1.3) for group differences in pre to post or pre to follow-up changes at a two-sided 5% significance of a 2-sample *t* test. While we may be underpowered to detect small to medium effects, the current pilot study will be crucial for informing the viability of the intervention and for estimating power for future, larger clinical trials.

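### The 80% power and margin-of-error figures use 45 or 19 degrees of freedom where eight randomized groups leave 6; power at the stated effects is about 67 to 69%

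*Protocol article*

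**What the plan says.** The Design section sets the number of randomized units: "Eighty participants will be recruited in eight groups", allocated 1:1. Randomization and blinding confirms that allocation is by group.

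The Sample size calculation starts "With total enrollment of *N* = 80 and an estimated 20% attrition rate", which leaves "32 subjects per group or 64 in total". It takes four clusters per arm with an average of 8 completers each and applies a design effect: "Considering a range of 0.05 to 0.3 for *ρ*, *n*_Eff_ will be somewhere between 10.3 and 23.7 per group".

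Two claims are then drawn from these effective sample sizes:

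- **Precision.** A half-width of 0.43 to 0.70, "times standard deviation as margin of error at 95% confidence for a continuous measure", from a t quantile on n − 1 degrees of freedom divided by √n.
- **Power.** "80% power to detect large effect sizes (*d* = 0.83 to 1.3) for group differences", at a "two-sided 5% significance of a 2-sample *t* test".

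The section concedes that power may be low for small to medium effects and says the pilot will help to estimate power for later, larger trials.

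**The concern.** The effective sample size says how variable an arm mean is under clustering. It does not say how well that variability can be estimated. When groups are randomized, the error for the arm comparison is estimated from differences between groups within an arm. With eight groups in two arms, that leaves 6 degrees of freedom, however many women are in each group. Using 2n_eff − 2 in place of 6 lowers the critical t from 2.447 to about 2.01 to 2.10, and this inflates the power.

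The margin of error has the parallel fault: n_eff − 1 degrees of freedom where four groups per arm leave 3. It also describes one arm's mean, whereas the primary hypothesis concerns the difference between arms.

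This is the protocol's only power statement, and it covers the primary outcome. A reader facing a null result would take it that effects of 0.83 to 1.3 SD had been tested with 80% power. A team planning the next group-randomized trial could carry over the same method.

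**Working it through.** **Inputs** (Sample size calculation; number of groups also in Design): m = 8 completers per group, k = 4 groups per arm, ρ = 0.05 to 0.3, two-sided α = 0.05, stated d = 0.83 and 1.3.

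**Step 1. Effective sample size per arm.** n_eff = mk/[1 + ρ(m − 1)] = 32/(1 + 7ρ).
- ρ = 0.05: 32/1.35 = 23.70
- ρ = 0.3: 32/3.10 = 10.32

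Both agree with the protocol.

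**Step 2. Reproduce the protocol's results.** Power comes from the non-central t with non-centrality d√(n_eff/2) and 2n_eff − 2 degrees of freedom. The margin is t(0.975; n_eff − 1)/√n_eff.

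| ρ | df | d at 80% power | power at stated d | margin (SD) |
|---|---|---|---|---|
| 0.05 | 45.4 | 0.832 | 79.9% | 0.425 |
| 0.3 | 18.6 | 1.301 | 79.9% | 0.700 |

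These match the printed 0.83 to 1.3 and 0.43 to 0.70. A normal approximation does not fit: it gives 81.5% and 84.0% power at the stated effects. So the protocol used a t test with degrees of freedom based on n_eff.

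**Step 3. Confirm that the standard error is right.** In SD units a group mean has variance ρ + (1 − ρ)/8, and the difference between two averages of four such means has variance 2/4 times that.
- ρ = 0.05: 0.05 + 0.95/8 = 0.16875; √(0.16875/2) = 0.290; √(2/23.70) = 0.290
- ρ = 0.3: 0.3 + 0.7/8 = 0.3875; √(0.3875/2) = 0.440; √(2/10.32) = 0.440

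The design-effect calculation and the comparison of 4 with 4 group means have the same standard error. Only the degrees of freedom differ, and for a comparison of eight group means they are 8 − 2 = 6.

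**Step 4. Recompute with 6 degrees of freedom.** The non-centrality is unchanged: 0.83 × √(23.70/2) = 2.86 and 1.3 × √(10.32/2) = 2.95. The critical t is 2.447.

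| ρ | power at stated d | d at 80% power |
|---|---|---|
| 0.05 | 66.6% (d = 0.83) | 0.978 |
| 0.3 | 69.4% (d = 1.3) | 1.482 |

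A simulation of t tests on 4 versus 4 group means (200,000 runs per setting) gave 66.6% and 69.4%. Type I error, simulated at ρ = 0.3, was 5.0%.

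**Step 5. Recompute the margins.**
- One arm's mean, k − 1 = 3 df, t = 3.182: 3.182/√23.70 = 0.654 and 3.182/√10.32 = 0.991
- Between-arm difference, 6 df: 2.447 × √(2/23.70) = 0.711 and 2.447 × √(2/10.32) = 1.077

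**The case against.** Several points can be made for the protocol.

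- **The arithmetic follows from the formula given.** True. Every printed figure reproduces, and the degrees of freedom used are already below the 62 that a raw count of completers would give. The fault lies in the reference distribution, not in a slip of calculation.
- **The planned analysis is a mixed model, not a t test.** This does not rescue the claim. Simulating a random group intercept that is dropped when its variance is estimated as zero gave 66.9% and 69.4% power. The Statistical analysis section also makes the group intercept optional, to be chosen by AIC or BIC. Omitting it when ρ > 0, as the sample size section assumes, raises nominal power only by giving up control of type I error.
- **The recomputed figures are conditional.** This stands. They assume equal groups of 8, the protocol's own ICC range and no covariate adjustment. Adjustment for age and IQ could reduce residual variance, but the sample size section claims no such gain. Adjusting for the two randomization blocks works the other way: 5 degrees of freedom give 63 to 66%.
- **One-arm precision is a legitimate choice for a pilot.** In part. The formula is printed and the text does not say that it is the margin for the difference. The degrees-of-freedom error applies to it all the same.
- **It is a pilot that admits limited power, and only large effects are detectable either way.** The admission concerns small to medium effects. The 80% claim is made for the large effects, and that is where it fails. It is also fair that the Statistical analysis section looks to observed effect sizes and attrition to guide later design, so the harm to the next trial is possible, not certain.

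**Conclusion.** The concern holds. Under the protocol's own inputs and a valid group-level test, power at the stated effects is 66.6% (d = 0.83, ρ = 0.05) and 69.4% (d = 1.3, ρ = 0.3), about 13 and 11 points below the stated 80%. The detectable range moves from 0.83–1.3 to 0.98–1.48, and the one-arm margin from 0.43–0.70 to 0.65–0.99 SD. That the margin is for one arm, not for the difference, is a secondary point. The main error should be corrected because the protocol asserts a power that the design does not deliver for its primary outcome.

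**What to change.** Restate the Sample size calculation along these lines: with four groups per arm, 8 completers per group and a t distribution on 6 degrees of freedom, power is 80% for d = 0.98 (ρ = 0.05) to d = 1.48 (ρ = 0.3), and the 95% margin of error for the between-group difference is 0.71 to 1.08 SD. If a one-arm margin is kept, give it as 0.65 to 0.99 SD on 3 degrees of freedom and label it as such. State that the figures assume equal group sizes and no covariate adjustment.

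A useful addition, though not required by the error itself, is to report the estimated intra-cluster correlation and a cluster-adjusted confidence interval beside each Cohen's d. The next trial would then not be planned from an imprecise point estimate alone.

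The cost is a change of text. The stated power and precision become less favourable; the sample size, primary outcome and conduct of the trial do not change.
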